#### Vital signs examination

2.9.2

Vital signs will be measured at baseline and at the first and second post-tests. The following parameters will be evaluated: systolic/diastolic blood pressure (measured after 5 min of sitting), pulse, and body temperature.

#### Concomitant medications

2.9.3

Patients undergoing conventional cognitive rehabilitation therapy will be able to participate in the trial without interrupting their therapy. Participants may be allowed to receive concomitant surgery, medication, or other medical devices only if the investigator believes that it will not affect the interpretation of the findings from the study. The investigator will assess the method and frequency of cognitive rehabilitation therapy as well as the type and dosage of all concomitant medications during the trial period at each visit and record them in a case record form (CRF) to monitor and identify adverse events. If the number of medications changes before and after participation in this study, a principal investigator will check for changes in the participant’s underlying medical condition. If the principal investigator determines that the change is a meaningful clinical change that could affect the study results, the data will be excluded from the main analysis group.

The number of participants, percentage, and number of concomitant medications will be reported and intergroup differences will be compared using the chi-square test (or Fisher’s exact test if the expected frequency is less than five cells and exceeds 20%). We will also analyze the correlation between the number and type of concomitant treatments and tDCS outcomes. Additionally, after standardizing the most recent version of the Anatomical Therapeutic Chemical Classification (ATC) code, the number of participants, percentages, and incidences of concomitant medication usage will be reported by group.

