#### Randomization

2.3.4

The participants will be randomized to the Optimized-tDCS and Sham-tDCS groups using a 1:1 ratio following the order of registration by a statistician who will not be involved in the application of the clinical trial. A stratified blocked randomization method with prespecified block sizes will be used. The stratification factor will be the hospital from which participants will be recruited. Random allocation numbers will be sealed in an opaque envelope and delivered to the medical device investigator who will administer the tDCS device in the hospital and will not be involved during the outcome measurement periods or other periods of the research.

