### Blinding

2.5

The participants and investigators in charge of performing the outcome measurements will remain unaware of the group allocation until the end of the study, and the data has been fully analyzed.

Owing to the nature of the study and individualized tDCS electrode localization, it is necessary that one investigator per hospital, in this case, the investigational device manager, remains unblinded during the investigation. The investigational device manager will be in charge of applying tDCS during the clinical trial; however, it will not be present during any outcome measurement period or at any other stage of the trial.

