### Statistical analyses

2.8

Descriptive statistics (average, standard deviation, median, minimum, and maximum) will be represented for each group for the changes found from baseline to the first and second post-tests. The Least Squares Mean (LSM) with a 95% confidence interval will be used to determine the trend of changes within time per group. The Shapiro–Wilk test will be used to determine data normality. If normality is met, the paired *t*-test will be used for within-group analysis at each time point; if normality is not met the Wil-coxon sign rank test will be performed. Following this, an independent *t*-test will be used for between-group analysis; if normality is not met, a Wilcoxon sign rank test would be performed. Additionally, an analysis of covariance (ANCOVA) with baseline as a covariate will be performed for a group × time analysis.

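### The main analysis drops participants on a principal investigator's judgement about medication changes after randomisation, so it no longer compares the groups as randomised

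*Protocol article*

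**What the plan says.** The rule is in section 2.9.3 (Concomitant medications) and has three steps.

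- Trigger: "If the number of medications changes before and after participation in this study, a principal investigator will check for changes" in the participant's underlying condition.
- Standard: "If the principal investigator determines that the change is a meaningful clinical change that could affect the study results".
- Consequence: the data leave the main analysis group ("could affect the study results, the data will be excluded from the main analysis group").

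The same section has type and dosage of all concomitant medications assessed at each visit and entered in the case record form.

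Section 2.3.4 sets up the comparison: "The participants will be randomized to the Optimized-tDCS and Sham-tDCS groups using a 1:1 ratio", stratified by hospital. In section 2.8, "an independent *t*-test will be used for between-group analysis" (with a non-parametric alternative), and an ANCOVA adjusts for baseline.

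On blinding, section 2.5 states: "The participants and investigators in charge of performing the outcome measurements will remain unaware of the group allocation". It adds that one investigator per hospital, "the investigational device manager, remains unblinded during the investigation", and keeps that person away from outcome measurement and every other stage. It does not mention the principal investigator who applies the rule in 2.9.3.

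**The concern.** Randomisation makes the two arms comparable at entry. That protection lasts only while participants are kept in the analysis for reasons unrelated to what happened afterwards. A new or stopped drug during the trial may follow cognitive decline, a change in mood or an adverse event, and each of these may differ by arm if stimulation does anything. Removing such participants makes membership of the main analysis depend on treatment and outcome. More participants would not cure the resulting bias. Blinding the decision would help but would not fully cure it: if stimulation changes who needs new medication, even blinded exclusions can be unbalanced.

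The standard adds to the problem because it asks whether the change could affect the results. The article gives no written criteria and no deadline. A comparison of medication before and after participation may be complete only once post-test scores exist.

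Two things are at stake. One is the optimized-versus-sham difference in ADAS-Cog and K-MMSE, the primary outcomes. The other is aim 3 in the Introduction, to obtain data for the sample size of a fully powered trial. That calculation uses the SD as well as the difference, and removing people from one tail lowers the SD.

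**Working it through.** **Inputs from the protocol article.** Section 2.7: minimum 32 participants, 20% dropout, 40 to be recruited. Section 2.3.4: 1:1 allocation, hence 16 per arm at 32. The article gives no SD, effect size or exclusion rate.

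**The plan's own figure.** 32 / (1 − 0.20) = 40, which reproduces. It allows for 40 − 32 = 8 losses and makes no separate allowance for exclusions under 2.9.3.

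**Assumptions for the illustration.** Change scores are normal with SD 1, higher is worse (as on ADAS-Cog), there is no true effect, and there are 16 per arm.

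**Standard error of the difference.** √(1/16 + 1/16) = 0.354 SD with nobody excluded.

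**One arm only, worst k removed.** The expected three largest of 16 standard normal values are 1.766, 1.285 and 0.990. The remaining mean shifts by their sum divided by the number left:

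- k = 1: 1.766 / 15 = 0.12 SD
- k = 2: (1.766 + 1.285) / 14 = 0.22 SD
- k = 3: (1.766 + 1.285 + 0.990) / 13 = 0.31 SD

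For k = 2 the ratio to the standard error is 0.218 / 0.354 = 0.62. With the standard error for 16 and 14, √(1/16 + 1/14) = 0.366, it is 0.60.

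**Between the extremes.** Suppose exclusions fall among the worst 20% of change scores, with the fraction of these removed differing by arm. Type I error is for a two-sided 5% test, by normal approximation, with the standard error held at 0.354:

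| Removed, active / sham | Bias (SD) | Type I error |
|---|---|---|
| 50% / 50% | 0 | 5% |
| 50% / 25% | 0.08 | 5.6% |
| 75% / 25% | 0.17 | 7.8% |
| 100% / 0% | 0.35 | 17% |

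The bias favours the arm that loses more of its decliners.

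**Effect on the SD.** By simulation, removing the worst 2 of 16 leaves an expected sample variance of about 0.71 in that arm. Pooled with an untouched arm this is (15 × 1 + 13 × 0.71) / 28 = 0.87; if both arms lose their worst two it is 0.71. Required sample size is proportional to variance for a fixed difference, so a later trial would be planned about 13% or 29% too small. Balanced exclusions therefore protect the difference but not the SD.

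**The case against.** The strongest reply is that the rule will rarely act and will act evenly. Inclusion criteria 5 and 6 require stable medication at entry, and treatment lasts about 8 weeks (3 + 2 + 3). A change in count only starts a review, which concerns the underlying medical condition rather than cognitive scores. The study is a feasibility trial with no powered test. All of this is fair and lowers the likely size, and the one-arm figures are a worst case. But the article does not ensure that exclusions are few, balanced or unrelated to outcome, and its primary outcomes are efficacy scales meant to inform a larger trial. A separate analysis plan may define analysis sets, but 2.9.3 is a stated rule that such a plan would be expected to follow.

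Four stronger readings are tempting, and the article does not support them.

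- *The decision-maker is unblinded.* The only site investigator named as unblinded is the device manager, whom 2.5 keeps out of all other stages, and the trial is called double-blind. The principal investigator may well be blinded. What stands is that neither this nor the timing of the decision is stated.
- *Each exclusion takes the trial below 32.* This happens only if dropouts and exclusions together exceed 8 of 40.
- *Adverse events are hidden.* Section 2.9.1 reports and tests them separately and does not limit them to the main analysis group. The worry is confined to the efficacy comparison.
- *Dose changes and switches go unseen.* They are recorded at each visit. The gap is narrower: "If the number of medications changes before and after participation in this study" is the only trigger for the exclusion review, so a dose change or one-for-one switch of a cognitive drug does not start it, although the entry criteria treat dosage as important.

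**Conclusion.** The concern holds. Section 2.9.3 lets a discretionary judgement made after randomisation decide who is in the main analysis, so the tests in 2.8 would not compare the groups as randomised. That follows from the text and needs no numerical assumption.

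The size cannot be derived from the article. Under the assumptions above, bias in the difference runs from about zero with symmetric exclusions to 0.12, 0.22 or 0.31 SD when the worst 1, 2 or 3 of 16 leave one arm only, two such exclusions being about 0.6 of a standard error. The zero holds only if both arms lose the same kind of participant at the same rate. The SD carried into aim 3 can be too small even then.

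The unstated blinding and timing of the decision and the count-only trigger are secondary weaknesses of the same rule.

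**What to change.** State in 2.8 and 2.9.3, and in the analysis plan, that the main analysis includes all randomised participants in their allocated arm, with all available outcome data, regardless of changes in medication. Take the future trial's difference and SD from that analysis.

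Keep the exclusion as a supplementary sensitivity analysis. Write its criteria in advance so that they cover dose changes and switches as well as changes in number. Have a blinded reviewer from existing study staff fix the list from those criteria before unblinding, and report the number excluded and the reasons by arm.

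The cost is a change of wording. No extra participants or visits are needed, and patient management is unaffected. The small downside is that the main estimate carries some noise from medication changes, which the sensitivity analysis can help to gauge.

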## Trial status

3

Participant recruitment began in August 2023 and is expected to be complete (including follow-up testing) by October 2024.

## Discussion

4

The present randomized double-blind controlled trial aims to prove the feasibility and safety of optimized tDCS in the treatment of patients with MCI-induced by AD for cognitive function improvement, throughout the use of 3D brain models based on personalized MRI scans to provide optimized tDCS electrode locations per participant.

The advancement of MCI induced by AD leads to great economic burden and limitations during daily life activities of the patients who suffer from it, who are commonly older adults who will require treatment for the rest of their lives (40). Hence, it is necessary to search for a treatment that aids in improving cognitive function while being safe for long-term use. Previous research has shown that tDCS can be safely used for 20 days and has significant effects on cognitive function (11, 12). Although there is a study that applied tDCS for 6 months in patients with MCI, more research is necessary because of the small sample size (41). Hence, the aim of the present study to apply tDCS to a relatively large sample of over 30 sessions, which is highly relevant for the future use of tDCS in this population.

tDCS has shown mixed results regarding its effectiveness in improving cognitive function. A recent study reported that tDCS over the DLPFC at 2 mA for 20 min in older adults with MCI due to AD effectively improved general cognition and immediate memory, as assessed using the MMSE (11). A systematic review showed that anodal tDCS may be an effective adjunctive therapy for patients with MCI (2). However, another systematic review reported inconsistencies regarding its effectiveness (8). Furthermore, a study applied tDCS twice a day for five consecutive days and found no significant changes following the results of ADAS-Cog and MMSE tests. The authors of a previous study hypothesized that the presence of patients with MCI and major cognitive disorders in the sample might have influenced the study results.

The results of past research and the inconsistencies reported in the systematic review can be attributed, in part, to inter-individual factors. The progression of MCI to a major cognitive disorder produces changes in certain brain structures (unique to each individual), such as generalized cortical atrophy characterized by reduced gyri volume, increased sulci width, and enlarged ventricles (especially the lateral ventricle) (15). Furthermore, an increase in the size of the ventricles appears to be a primary sign or secondary effect associated with atrophy of the periventricular parenchyma (15). Brain tissue atrophy caused by age-related changes and conditions, such as MCI, can disrupt current tDCS pathways. To investigate this further, one study used three structural MRI scans to develop 3D brain models representing a young adult, an older adult, and an MCI patient and subsequently applied the same tDCS protocol to each of the models. They found that the maximum current density in the cortical tissue decreased according to the degree of GM atrophy (42).

Therefore, it is clear why individual brain characteristics must be considered when designing tDCS interventions. MRI-based 3D brain models for optimized tDCS electrode location may be a solution for these inter-individual factors; hence, the application of this study will be of significant importance for the future use of tDCS in this population and the assessment of its effects.

According to previous research, the use of a fixed, classic location for the tDCS electrodes does not consider individual differences in anatomy, limiting the amount of current reaching the brain and causing variability in the E-field at the cortical target site, influencing the tDCS effects (43). One study assessed the correlation between E-field strength and the improvement of working memory (WM) in older adults after 10 sessions of 2 mA tDCS over the classic DLPFC locations, finding that participants with an E-field higher than average within the study sample had an increased WM improvement after the intervention (44). Although it is a different population, these results prove that ensuring the most adequate E-field per person could positively impact the effectiveness of tDCS applied to the DLPFC.

In addition, recent research has found that age and biological sex influence the current density at a target point. A study using 3D modeling based on approximately 700 individuals’ MRIs determined that older female adults received a higher simulated current at the DLPFC target area than their counterparts using the same tDCS protocol. They concluded that individual modeling is required to account for the variability in cortical morphometry and to adjust the stimulation parameters of tDCS to achieve the intended stimulation benefits (45).

Moreover, the effect of tDCS is influenced by electrode characteristics (46). Generally, most tDCS studies have used electrode sizes of 25 cm^2^ to 35 cm^2^ with currents between 1 and 3 mA and a duration of 20–30 min. Large electrodes stimulate large regions of the brain and computer simulation studies have shown no focal current density distribution. In addition, these electrodes contribute to the edge effect, which is the current concentration at the edges of the electrodes at the corners of the rectangular and square electrodes. Using smaller and circular electrodes may help decrease edge effects and improve the focus of the current in the target area (46). Therefore, 1.5 cm disk electrodes will be employed in this study.

The use of tDCS for 20 days in patients with MCI has been proven to be safe (5). Moreover, one study safely applied tDCS for six months in patients with AD at an intensity of 2 mA for 30 min (41). However, these previous studies used wider electrodes (rectangular 7 × 5 cm and round 6 cm diameter, respectively) than those used in the present study. In a study with healthy volunteers, one session of 1 mA for 12 min was applied using electrodes (3.14 cm^2^) to the sensorimotor area without reporting adverse effects; to the best of our knowledge, this is the only study that used two electrodes of a similar small size to ours (47). Our study will use small disk electrodes for a relatively long period (30 sessions in total); therefore, as the safety of this electrode size in an MCI population has not yet been reported, the decision to divide the 30 sessions into two blocks of 15 sessions with a resting period in between was made.

According to a previous study, five consecutive sessions of tDCS in patients with MCI at 2 mA for 20 min over F3 significantly improved delayed recall, with results persisting after one month of follow-up (48). Another study applied tDCS in patients with AD for 25 min daily (10 sessions) at 2 mA to determine its effectiveness in treating cognitive decline, and found that the MMSE scores showed significant changes that were maintained at 1 and 2 months after the intervention (49). According to previous research, the effects of tDCS can be maintained for at least one month after five sessions, which shows that a resting period of two weeks is sufficient without diminishing the effectiveness of tDCS.

To the best of our knowledge, personalized bilateral optimization of tDCS in patients with AD-induced MCI has not been reported. Nevertheless, a similar study applied six sessions of personalized optimized anodal high-definition tDCS at 2 mA for 20 min to adults with AD, which resulted in significant improvement of the MMSE scores in comparison with the sham group (16). However, we believe that the validity of bilateral tDCS with two electrodes still needs to be validated and this trial aims to validate the safety and efficacy of personalized tDCS as a new tDCS protocol.

The trial presents various limitations. First, the absence of a group using conventional tDCS electrode locations guided by the 10–20 EEG-based system for comparison between optimized and conventional tDCS electrode locations. After concluding this trial, we will consider including a conventional tDCS group in future studies. Second, no previous studies have directly supported the safety of the electrode type chosen in this study. Nevertheless, this study will be able to validate its efficacy and safety relative to sham tDCS. Third, the absence of a follow-up evaluation to determine if the effectiveness of the treatment will be maintained in time. A follow-up evaluation will be considered in future fully powered trials.

For this present study, we hypothesize that the participants will tolerate the optimized tDCS intervention without any significant adverse effects, and that, compared to the sham tDCS group, the optimized personalized tDCS application will affect the treatment of patients with MCI-induced AD for cognitive function.

## Ethics and dissemination

5

This protocol was approved by the MFDS and will be conducted according to the ethical standards of the 1964 Declaration of Helsinki. The protocol was approved by the Ethics Review Boards of the three universities mentioned in the Methods and Analysis section. In addition, the participants will sign an informed consent form to participate in the intervention.

## Ethics statement

This protocol was approved by the Korean Ministry of Food and Drug Safety (MFDS) and will be conducted in accordance with the ethical standards of the 1964 Declaration of Helsinki. Additionally, the protocol was approved under the number XC23DSDS0053 by the Integrated Ethics Review Boards of the following universities: Catholic University of Korea, Yeouido St. Mary’s Hospital, Catholic University of Korea, Seoul St. Mary’s Hospital and Catholic University of Korea, St. Vincent’s Hospital. Participants will sign an informed consent form after receiving a full description of the study’s objectives, benefits, and any potential discomfort they might experience during the intervention.
